Study type	Allocation: non-randomized Intervention model: parallel assignment Primary purpose: treatment
Date of first enrollment	December, 2024.
Target sample size	36
Recruitment status	Recruiting.
Primary outcome(s)	Method of measurement: Biopotentials (ECG, PCG, EDA, fNIRS, respiratory rhythm) Timepoint: pre-treatment, post-treatment, and follow-up.
Key secondary outcomes	Changes in neuroimaging measures Timepoint: pre-treatment, post-treatment, and follow-up. Changes in biopotential measures Timepoint: pre-treatment, post-treatment, and follow-up.
Ethics Review	This project received ethical approval from Harran University with the decision of the clinical research ethics committee on 03 July 2024.
Completion Date	October, 2025

The SPIRIT reporting guidelines recommend these items to be included in trial protocols to provide a brief, structured overview of a trial.

Our study is a non-randomized, parallel-group cohort study. Patients were assigned to a group in the chronological order of enrollment in the study. Therefore, consecutive sampling was used for allocation concealment. The inclusion and exclusion criteria will be applied uniformly to all patients, regardless of group, without exception. At inclusion, baseline characteristics will be compared between groups, including age, sex, and whether participants experienced the earthquake as a traumatic event. The comparability of the groups at inclusion will be verified by ensuring that there are no significant differences between groups.

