#### Inclusion criteria

3.1.1

Young earthquake survivors without specific diseases who recently experienced the earthquake in our region in February 2023 will be selected. The sample sizes of 20–25 participants have been selected in similar studies (Maheu et al., 2005; Nakajima et al., 2016; Tegeler et al., 2023; Zabrecky et al., 2020). The sample size selected (*n* = 10–12 participants per group) follows the rule of thumb proposed by Julious (2005), which is widely recognized in the methodological literature as a minimum standard for pilot studies (Julious, 2005). Furthermore, our proposal will use deep learning and current artificial intelligence algorithms. Because data can be obtained from each measurement within the time-series dataset used for this purpose, a substantial amount of data can be generated through windowing and data augmentation, and transfer learning can be performed; it is assumed that a dataset from 36 participants will be sufficient. Consequently, at least 30 university students aged between 20 and 25 years who experienced and survived the earthquake will take part in the experiment. They must have experienced the earthquake as a significant and severe event. In accordance with the inclusion criteria, the participants will be healthy, non-obese men (*n* = 18) and women (*n* = 18). In particular, all participants should have experienced the earthquake disaster in the local region. All participants must be free of any chronic or acute infection, neurological, psychiatric, and/or cardiovascular disease. They must be non-smokers, have no alcohol or drug addiction, and not be under any medical treatment. Pregnant or breastfeeding women will not be included in the study.

University students who survived the earthquake in the region will be invited to volunteer for this study. The inclusion and exclusion criteria will be verified by interviewing the volunteers. Participants will then undergo a medical examination by a psychiatrist. If no problems are found, participants will be recruited for the study.

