#### Study design

3.1.2

An intervention and control group will be formed with 20 and 10 participants, respectively. The intervention and control groups will be exposed to the same mental stress.

*Control group:* 10 young healthy earthquake survivors will not receive any auditory stimulation.

Intervention group: 10 young healthy earthquake survivors will be subjected to closed-loop, real-time heart sound (PCG) stimulation to create biofeedback.Intervention group: 10 young healthy earthquake survivors will be given an auditory stimulus of their heart sound and a metronome synchronized with their mean heart rate (MHR) recorded during a calm state.

Participants will be taken individually to the experimental room and seated comfortably in a quiet and spacious environment. Before the first session, a scientific introduction, the purpose of the study, an explanation of how it will be conducted, an explanation of the mental stress to be induced, and basic information about the measurements to be taken will be provided at the information meeting (using an introduction video). The participant should feel as comfortable as possible, and no additional sources of stress should be created. Participants will be instructed to breathe normally and avoid moving their legs.

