From the study of Gerdes et al., public treatment centers called “Cereset” were opened on the American and European continents. Similar to physiotherapy centers, these centers offer relaxation methods over 10 sessions within 4 weeks by acting on the patient’s parasympathetic system using EEG signals (Tegeler et al., 2023). For post-traumatic therapy sessions, 10 sessions of 30 min each are considered sufficient (Desbiendras, 2024). In this context, the participants will have 10 sessions over approximately 4 weeks (S1-S10). According to the literature, 10 sessions are sufficient for effective intervention and adequate observation. Participants will receive the first two sessions on consecutive days. Then, participants will have two sessions in a half-day period with a 1-h break between sessions. Participants will receive the third session within the first 5 days. Participants will complete the rest of the 10 sessions, with a maximum of 5 days between sessions. The sessions will occur between 1:00 and 5:00 p.m. ±30 min, as the participants may better remember emotionally stimulating information in the afternoon (Maheu et al., 2005). In addition, according to Figures 1–3, the transitions between stages will be direct and immediate without a break. In addition, the date of menstrual onset will be recorded to account for the menstrual periods of female participants.

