#### Statistical methods

3.5.1

RMSSD, HF, and LF derived from HRV will be the primary pilot outcomes for estimating the effect size and variance, with a view to calculating the sample size for a future confirmatory trial. The primary outcomes will be assessed at the final session and compared with those obtained at the first session. The analyses will be conducted using a linear mixed-model (LMM), with group and time as fixed effects or using an analysis of covariance (ANCOVA). Other measures, such as electrodermal activity, respiratory rate, and neuroimaging, will be treated as secondary endpoints for exploratory purposes.

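### The 18/18 sex quota applies only to the whole sample; arms follow enrolment order and the stated mixed model has no sex term, so sex can differ between arms unadjusted (modest effect)

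*Protocol article*

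**What the plan says.** - **Sex quota.** Section 3.1.1 (Inclusion criteria), repeated in Table 1: "the participants will be healthy, non-obese men (*n* = 18) and women (*n* = 18". It is given for the whole sample of 36.
- **Allocation.** Section 3 (Methods/design): "Our study is a non-randomized, parallel-group cohort study", and "Patients were assigned to a group in the chronological order of enrollment in the study". No stratum or quota by sex is stated.
- **Arm sizes.** Section 3.1.1 says "The sample size selected (*n* = 10–12 participants per group) follows the rule of thumb proposed by Julious (2005". Section 3.1.2 (Study design) says "An intervention and control group will be formed with 20 and 10 participants, respectively". Neither gives a sex split by arm.
- **Primary analysis.** Section 3.5.1 takes RMSSD, HF and LF, compares the final session with the first, and specifies a linear mixed model "with group and time as fixed effects or using an analysis of covariance (ANCOVA". No covariate is named for the ANCOVA.
- **Provision on sex between arms.** Section 3 also says that baseline characteristics, sex among them, will be compared between the groups. It treats the absence of a significant difference as verification that the groups are comparable. It states no action if a difference is found.

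**The concern.** A quota on the total does not by itself balance a comparison between arms. Balance has to hold within each arm, or the analysis has to adjust for its absence. In the stated design the quota acts on who enters, enrolment order decides who goes where, and the named fixed effects leave sex out. If men and women differ in how these outcomes change over ten sessions, an uneven sex mix moves the between-arm contrast by an amount unrelated to the stimulation. The pilot exists to supply an effect size and variance for a later trial, so such a shift would pass into that trial's sample size.

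**Working it through.** **Inputs.** 18 men and 18 women (3.1.1, Table 1); three arms; 10 to 12 per arm (3.1.1) or 10 per arm (3.1.2). Assumptions not in the document: enrolment order unrelated to sex; a 15/15 split if the total is 30; two-sided 0.05 for the baseline check; a sex difference in change of 0.3 to 0.6 SD.

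**1. The plan's own figure.** 3 × 12 = 36 = 18 + 18, so the quota reproduces with 12 per arm. With 10 per arm the total is 30, which matches the stated minimum but not 18 + 18. Both sizes are therefore shown.

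**2. Sex mix by arm.** If order is unrelated to sex, the numbers of women (a, b, c) in three arms of 12 have probability

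P(a, b, c) = C(12,a) · C(12,b) · C(12,c) / C(36,18), with a + b + c = 18.

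All arms 6:6: 924³ / 9,075,135,300 = 0.087. Summing the other terms gives:

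| | 12 per arm (18/18) | 10 per arm (15/15 assumed) |
|---|---|---|
| All arms exactly balanced | 0.087 | 0.103 |
| A given pair differs by 3 or more | 0.314 | 0.272 |
| A given pair differs by 4 or more | 0.158 | 0.122 |
| Some pair of the three differs by 4 or more | 0.325 | 0.262 |

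The given-pair row is the one that belongs with a single treatment contrast.

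**3. Would the baseline check catch it?** Fisher exact test, two arms of 12:
- 8 v 4: p = 0.22
- 9 v 4: p = 0.10
- 9 v 3: p = 0.039

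A given pair reaches p < 0.05 in 2.5% of allocations, and only when the gap is 6 or more. Of allocations in which that pair differs by 4 or more, 0.0247 / 0.1576 = 16% would be flagged.

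For a three-arm chi-square, 8/6/4 gives (4 + 0 + 4)/6 × 2 = 2.67 on 2 df, p = 0.26. Of allocations in which some pair differs by 4 or more, it flags 0.0609 / 0.3246 = 19% (10 per arm: 0.0342 / 0.2623 = 13%).

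**4. Size of the shift.** Shift = (difference in number of women / arm size) × sex difference in change. For 8 v 4 this is 4/12 = 0.33 of that difference:
- 0.33 × 0.3 SD = 0.10 SD
- 0.33 × 0.6 SD = 0.20 SD

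The standard error of a two-arm contrast with 12 per arm is √(2/12) = 0.41 SD.

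**5. Which model term removes it?** Take the treatment effect as the group-by-time term, since 3.5.1 compares final with first session. With two complete time points its estimate is the difference between arms in mean change. A sex main effect adds the same amount at both sessions and drops out of each person's change, so the estimate does not move. In a simulated complete data set with an 8 v 4 split, the estimate was 0.467 both without sex and with a sex main effect. It became 0.274 once sex-by-time was added. In an ANCOVA on the final-session value with the first-session value as covariate, a sex covariate adjusts the contrast directly.

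**The case against.** **The protocol does address sex.** It compares sex between groups at baseline. That is so, and reporting the mix is useful. But the comparison creates no balance, leads to no stated action, and at this size would usually pass an uneven split as comparable (step 3).

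**The covariate list may be in an analysis plan not shown.** This stands in part. The ANCOVA covariates are unnamed, and section 5 mentions a statistical analysis plan. The mixed model's fixed effects are, however, written out here without sex. The statement about the model is therefore about this text only.

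**The shift is small.** A constant sex difference in level largely cancels in final versus first, so only a sex difference in change matters, and the document gives no figure for one. At 0.10 to 0.20 SD the shift is well inside the standard error of 0.41 SD. If order is unrelated to sex, it is a chance imbalance with no fixed direction. All of this stands and limits the point.

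**Stronger readings that the document does not support:**
- *The chance of a serious imbalance is one in three.* The 0.32 is for the widest gap among three arms; for one contrast it is 0.16.
- *Filling one sex's quota first must worsen balance.* That depends on whether arms were filled in rotation or one after another, which is not stated. If 70% of volunteers were of one sex (assumed), simulation gives a probability of about 0.17 under rotation, and about 0.91 under sequential filling, that some pair differs by 4 or more.
- *The quota achieves nothing.* It secures both sexes in the sample and, if order is unrelated to sex, 6:6 per arm on average.
- *The menstrual record shows that arms were meant to be balanced by sex.* Section 3.1.2 says only that "the date of menstrual onset will be recorded to account for the menstrual periods of female participants", which concerns timing within women.

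**Conclusion.** The concern holds in a limited form. The quota is set for the total only, arms follow enrolment order, and the stated mixed model does not adjust for sex. With 12 per arm and order unrelated to sex, about one contrast in six would have a gap of 4 or more women, and the baseline test would rarely flag it. The consequence is a shift of one third of any sex difference in change, 0.10 to 0.20 SD under the assumed 0.3 to 0.6 SD. This is a precision and interpretability issue in a pilot; the document does not show that any estimate is in fact biased by sex. It is worth correcting because sex is already recorded and the adjustment is nearly free.

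**What to change.** In 3.5.1, specify one of the following:
- ANCOVA on the final-session value, with group, the first-session value and sex; or
- the mixed model with group, time, group-by-time, sex and sex-by-time. A sex main effect alone is not enough (step 5).

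In section 3, report the number of men and women in each arm, and do not rely on a non-significant test as evidence of comparability.

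A per-arm quota is largely out of reach, since section 3 says that data collection was completed by 30 June 2025. For anyone still to be assigned, including the 10 backup participants in section 5, assign within sex so as to equalise men and women per arm.

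Cost: one degree of freedom in the ANCOVA or two in the mixed model, and no new data.

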#### Study design

3.1.2

An intervention and control group will be formed with 20 and 10 participants, respectively. The intervention and control groups will be exposed to the same mental stress.

*Control group:* 10 young healthy earthquake survivors will not receive any auditory stimulation.

Intervention group: 10 young healthy earthquake survivors will be subjected to closed-loop, real-time heart sound (PCG) stimulation to create biofeedback.Intervention group: 10 young healthy earthquake survivors will be given an auditory stimulus of their heart sound and a metronome synchronized with their mean heart rate (MHR) recorded during a calm state.

Participants will be taken individually to the experimental room and seated comfortably in a quiet and spacious environment. Before the first session, a scientific introduction, the purpose of the study, an explanation of how it will be conducted, an explanation of the mental stress to be induced, and basic information about the measurements to be taken will be provided at the information meeting (using an introduction video). The participant should feel as comfortable as possible, and no additional sources of stress should be created. Participants will be instructed to breathe normally and avoid moving their legs.

From the study of Gerdes et al., public treatment centers called “Cereset” were opened on the American and European continents. Similar to physiotherapy centers, these centers offer relaxation methods over 10 sessions within 4 weeks by acting on the patient’s parasympathetic system using EEG signals (Tegeler et al., 2023). For post-traumatic therapy sessions, 10 sessions of 30 min each are considered sufficient (Desbiendras, 2024). In this context, the participants will have 10 sessions over approximately 4 weeks (S1-S10). According to the literature, 10 sessions are sufficient for effective intervention and adequate observation. Participants will receive the first two sessions on consecutive days. Then, participants will have two sessions in a half-day period with a 1-h break between sessions. Participants will receive the third session within the first 5 days. Participants will complete the rest of the 10 sessions, with a maximum of 5 days between sessions. The sessions will occur between 1:00 and 5:00 p.m. ±30 min, as the participants may better remember emotionally stimulating information in the afternoon (Maheu et al., 2005). In addition, according to Figures 1–3, the transitions between stages will be direct and immediate without a break. In addition, the date of menstrual onset will be recorded to account for the menstrual periods of female participants.

**Figure 1 fig1:**

Procedure to be applied to all groups before the first session.

**Figure 2 fig2:**
[figure not shown]
Procedure to be applied in each session (10 sessions). MHR: Stimulation at Mean Heart Rate; PCG: real-time and closed-loop heart sound stimulation.

**Figure 3 fig3:**

After 4 weeks, the procedure to be applied to all groups.

In this context, earthquake victims’ emotional and psychological states will be monitored using biomedical signals, and responses will be derived from these signals. Respiratory rhythm, electrocardiography (ECG), phonocardiography (PCG) (Özcan, 2024), electrodermal activity (EDA), and functional near-infrared spectroscopy (fNIRS) measurements will be performed during the information session, at the beginning of the sessions, throughout the 10 intervention sessions, and 4 weeks after the intervention (Arsalan et al., 2023). The application after about 4 weeks is to see whether the intervention is permanent.

Stress, anxiety, and depression will be assessed using psycho-emotional stressors at the beginning and end of the intervention using the Turkish version of the Depression Anxiety Stress Scale–21 (DASÖ-21) (Yıldırım et al., 2018).

Live heart sounds or average heartbeat sounds will be used as stimuli to provide biofeedback. A metronome will also be used for the auditory stimuli, including the heart rate from the ECG and the measured phonocardiogram. The audio stimulus will be presented at an intensity of 60–65 ± 10 dB before and during mental stress.

Different mental stress tasks will be induced in all sessions and 4 weeks after the sessions. A mental arithmetic task is a mechanism that increases the mental workload by performing a series of arithmetic operations of varying degrees of difficulty. One of the effective platforms used in the literature is Millisecond (Millisecond Software, Seattle, WA, USA), and the Trier Mental Challenge Test (TMCT) available through the Inquisit application will be used in the study. Millisecond Software is a leading software provider for psychological testing. The Inquisit platform has been used in applied fields, such as clinical trials, and several peer-reviewed studies. The TMCT is a timed arithmetic test designed by Kirschbaum to induce psychological stress in participants (Kirschbaum, 1991). During the session and throughout the 10 sessions, the mental operations should be randomized in order to create stress without allowing learning to occur.

Deep learning techniques and statistical analyses will be used to examine the causality between the generated stress, given warning, and measurements. The data will be processed as a time series or converted into images in our study. Each participant will have 390 min of experimental activity, including 330 min of measurement time.

Transfer learning from an existing pretrained convolutional neural networks (CNNs) will be applied for the acquired data. If there is sufficient data to train a new neural network, the formation of a new network architecture is considered for the sustainability of the protocol.

Explainable artificial intelligence techniques will be used to analyze the data attributes used by the network.

Below are the protocol diagrams to be applied before the first session, throughout the 10 intervention sessions, and after 4 weeks (Figures 1–3).

### Data acquisition device

3.2

Continuous monitoring of physiological signals, including respiratory rhythm, electrocardiogram (ECG), phonocardiogram, and electrodermal activity, will be performed using the BIOPAC System.

The fNIRS device from BIPAC will measure oxygenated and deoxygenated hemoglobin concentrations in the cortical brain structure during mental exertion (Santosa et al., 2014).

### Relative measurements/parameters

3.3

The parameters obtained from the measurements and their meanings are summarized below.

Heart rate, heart rate variability (HRV), low-frequency band (LF), high-frequency band (HF) components of the HRV signal, the LF/HF ratio, and HFnu = HF/LF + HF (normalized unit) will be calculated.Standard indices of vagal control: The root mean square successive differences (RMSSD) between RR intervals, standard deviation of normal-to-normal (NN) intervals representing standard deviation of normal-to-normal (NN) intervals (SDNN), and percentage of consecutive regular sinus RR intervals of more than 50 ms (pNN50; Laborde et al., 2017) will be calculated.Galvanic skin response, including EDA/skin conductance level (SCL) and event-related skin conductance responses (SCRs) attributable to a specific stimulus, will be used as parameters (Braithwaite et al., 2015).Oxygenated hemoglobin concentration (HbO), deoxygenated hemoglobin concentration (HbR), total hemoglobin concentration (HbT = HbO + HbR), and oxygen consumption (Oxy = HbO - HbR) will be used as parameters derived from fNIRS data (Ghosh, 2024).

### Data analysis

3.4

Mood assessment will be conducted as described below using methods to analyze pre- and post-treatment questionnaires and by examining changes in parameters derived from biological signals (RMSSD, LF, HF, LF/HF, SDNN, SCL, SCR, and respiratory rate). Statistical methods will be used to analyze and evaluate the data obtained from the collected stress and anxiety questionnaires. In addition to respiratory rate, ECG, PCG, EDR signals, heart rate, heart rate variability (HRV), low-frequency band (LF) and high-frequency band (HF) indicators from the HRV signal, the LF/HF ratio, SDNN, RMSSD, and pNN50 parameters will be processed. Functional NIRS will be used to monitor brain functions in real time. These analyses will be based on changes in oxygenated and deoxygenated hemoglobin concentrations in the cerebral cortex. In particular, the prefrontal cortex region and limbic lobe (Balters et al., 2021; Dattola et al., 2023) will be monitored. Changes in the obtained signals and parameters change before, during, and after the intervention will be analyzed. Statistical techniques, deep learning, and explainable artificial intelligence (XAI) techniques will be used for this purpose. To evaluate the benefits and differences of the biofeedback study, classification analyses will be performed on the data.

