#### Phonocardiogram data and fNIRS data

3.4.1

Heart sounds to be used as stimuli and for monitoring purposes will be converted into Mel spectrograms and input into neural networks trained with sound (OpenL3, YAMNet, and VGGish), and transfer learning will be performed.

Cognitive assessment will be performed by analyzing fNIRS signals to assess activation in specific brain regions (right, center, and left). The details are provided below. During mental stress, classification analyses will be performed between the results between the control and treatment groups and between the results of the same group before and after treatment. Then, using explainable artificial intelligence (XAI) techniques, the temporal and frequency-domain characteristics associated with these changes will be evaluated.

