#### ECG, EDR, and fNIRS data

3.4.2

The data obtained using deep learning techniques will be classified. Classification studies will be performed with deep learning to emphasize to characterize differences between the control and treatment groups, as well as differences before and after treatment within groups and to show that the difference is significant. The data will be converted into spectrogram images and processed as time-series data. A suitable pretrained network (AlexNet, SqueezeNet, GoogLeNet, etc.) will be used with transfer learning, and classification will be performed. Technical information is provided in our published articles (Özcan and Alkan, 2021, 2023a, 2023b).

On the other hand, correlation analysis will be performed using deep learning method (Alessandrini et al., 2023). Then, the features used in the classification will be evaluated using explainable artificial intelligence techniques.

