Transfer learning will provide faster and more effective learning algorithms by reducing the size of the dataset. The network will be fine-tuned with transfer learning, and feature extraction will be performed quickly. The dataset will be expanded using smaller time windows of the signals. If we divide 330 min of recordings into 10-s segments, 1980 time series or representative images will be processed for each measurement. In addition, the dataset can be expanded using the data augmentation technique. Data from 36 subjects would be sufficient in this case. Of the dataset, 70% will be used for training the neural network, 15% for validation, and 15% for testing. To ensure that the training and test sets are created on an individual basis, we would need a larger number of participants. This could be the subject of future studies.

Despite their excellent performance, deep learning models produce good results without being able to explain why. These models act as a black box for users. This is one of the main limitations of deep learning in medicine. Therefore, the issue of the explainability of neural networks has emerged (Ilias and Askounis, 2022; Ong et al., 2021; Thibeau-Sutre et al., 2023). The behavior and reasons for the importance of features automatically used in artificial intelligence tools will thus be understood (Ong et al., 2021). The XAI framework will use different techniques, such as LIME (Local Interpretable Model-agnostic Explanations), Occlusion Sensitivity, and Grad-CAM. These methods, each with a specific approach to classifying an image, produce a map showing the regions of the image that are important for the process. The network will use these maps for decision-making.

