#### Performance metrics

3.5.3

The proposed methods’ accuracy, sensitivity, specificity, precision, and F1-score (Table 2) will be measured as evaluation parameters. A confusion matrix will also be extracted to provide an overview. An optimization study will be performed to determine the best hyperparameter settings. Five cross-validation will be selected, and the average values of the results will be obtained. The methods with the highest performance will be compared with the others.

**Table 2 tab2:** Calculations of performance metrics (Özcan and Alkan, 2021, 2023a, 2023b).

Accuracy	Sensitivity	Specificity	Precision	F1 score
$\frac{\mathrm{TP}+\mathrm{TN}}{\mathrm{TP}+\mathrm{TN}+\mathrm{FP}+\mathrm{FN}}$	$\frac{\mathrm{TP}}{\mathrm{TP}+\mathrm{FN}}$	$\frac{\mathrm{TN}}{\mathrm{TN}+\mathrm{FP}}$	$\frac{\mathrm{TP}}{\mathrm{TP}+\mathrm{FP}}$	$\frac{2\mathrm{TP}}{2\mathrm{TP}+\mathrm{FP}+\mathrm{FN}}$

TP: true positive; FN: false negative; FP: false positive; TN: true negative.

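### Classification is asked to show benefit and significance, but the planned metrics have no direction and test nothing, and the segment-level split inflates them

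*Protocol article*

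**What the plan says.** Two sentences in the protocol article give classification an inferential job.

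- Section 3.4 (Data analysis): "To evaluate the benefits and differences of the biofeedback study, classification analyses will be performed on the data".
- Section 3.4.2 (ECG, EDR, and fNIRS data) says deep-learning classification will characterise control-versus-treatment differences as well as "differences before and after treatment within groups and to show that the difference is significant".

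Section 3.4.1 plans the same two contrasts for signals recorded in the stress task. Between arms, "classification analyses will be performed between the results between the control and treatment groups"; within an arm, post-intervention results are set against pre-intervention ones.

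The classifiers are to be judged as set out in 3.5.3 (Performance metrics): "accuracy, sensitivity, specificity, precision, and F1-score (Table 2) will be measured as evaluation parameters". A confusion matrix is added, and "Five cross-validation will be selected, and the average values of the results will be obtained".

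Section 3.5.2 describes the data that feed these metrics: "If we divide 330 min of recordings into 10-s segments, 1980 time series or representative images will be processed for each measurement". The split is 70% training, 15% validation and 15% test. On the unit of that split it says: "To ensure that the training and test sets are created on an individual basis, we would need a larger number of participants", and leaves the matter to future studies.

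Separately, 3.5.1 (Statistical methods) analyses the primary outcomes RMSSD, HF and LF by a linear mixed model or ANCOVA.

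**The concern.** Three separate problems prevent classification from doing the job it is given.

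1. **No direction.** Accuracy, sensitivity, specificity, precision and F1 are all functions of TP, TN, FP and FN. They record how often the predicted label matches the true one. They do not record whether the treated group was calmer or more stressed.
2. **No test.** None of these metrics is a significance test, and averaging over five folds does not make one.
3. **Leakage of identity.** Each participant belongs to one arm only. If segments from the same person fall in both the training and test sets, recognising the person is enough to name the arm. High control-versus-treatment accuracy can then arise with no arm effect.

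A report that followed 3.4 and 3.4.2 as written could present high classifier accuracy as evidence that biofeedback helps, or that the arms differ significantly. It would support neither statement.

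**Working it through.** **The plan's own figure.** 330 min × 60 s ÷ 10 s = 1,980 segments per participant per measurement, as stated in 3.5.2.

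**Direction.** Suppose treatment shifts the features by +d in one scenario and by −d in another. The groups are equally far apart in both, so the counts TP, TN, FP and FN have the same distribution. A simulation at ±0.5 SD on all features (10 v 10, between-participant share 0.5) agrees:

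| Metric | +0.5 SD | −0.5 SD |
|---|---|---|
| Accuracy | 0.889 | 0.888 |
| Sensitivity | 0.891 | 0.890 |
| Specificity | 0.889 | 0.887 |
| Precision | 0.889 | 0.887 |
| F1 | 0.889 | 0.888 |

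**Leakage, control versus treatment.**

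- From the plan: three groups of 10 (3.1.2), so 10 v 10 for one intervention arm against control and 20 v 10 for both pooled; a 70/15/15 split not made by individual (3.5.2); KNN as one of the named classifiers (3.4.3).
- Assumed: 10 independent normal features with total variance 1; 60 segments per participant; 5 nearest neighbours; 400 runs (200 with participants held out).
- Model for participant i, segment j: x_ij = b_i + e_ij, with Var(b) = ρ, Var(e) = 1 − ρ and **no arm effect**. The plan gives no value for ρ, so it was varied.

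Mean test accuracy with no arm effect:

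| Comparison | Split | ρ = 0.3 | ρ = 0.5 | ρ = 0.7 |
|---|---|---|---|---|
| 10 v 10 | by segment | 0.651 | 0.816 | 0.957 |
| 10 v 10 | by participant | 0.495 | 0.504 | 0.498 |
| 20 v 10 | by segment | 0.685 | 0.813 | 0.951 |
| 20 v 10 | by participant | 0.551 | 0.553 | 0.546 |

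The no-information benchmark is 0.50 for 10 v 10 and 20/30 = 0.67 for 20 v 10. With 36 participants and ρ = 0.5, the segment split gives 0.806 (12 v 12) and 0.801 (24 v 12). A second run for 10 v 10 (100 replicates) extended the range downwards: 0.50 at ρ = 0 and 0.54 at ρ = 0.1.

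**Significance.** Two arms of 10 give 20 × 1,980 = 39,600 segments, of which 15% is 5,940 test segments. If these were treated as independent, SE = √(0.25/5,940) = 0.0065, and any accuracy above 0.5 + 1.645 × 0.0065 = 0.511 would look significant at one-sided 5%. The plan does not propose this test. The figure shows only how little accuracy above 0.5 means when segments are taken as the sample size.

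**Before versus after within a group.** Here each participant contributes to both classes, so recognising the person does not reveal the label. With 10 participants and no time effect, accuracy was 0.496 when there was no session-to-session variation. It was 0.676, 0.751 and 0.862 when a participant-by-session component took 0.1, 0.2 and 0.3 of the variance. Distortion of this contrast therefore depends on such variation being present.

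**The case against.** The strongest reply is that classification is not the operative inferential plan. Section 3.5.1 assigns the primary outcomes to a mixed model or ANCOVA for estimating effect size and variance. Section 3.4 also lists statistical techniques beside deep learning. The Limitations section calls the study preliminary, and the sentence in 3.4.2 is garbled enough that its reference to significance may be loose wording. A chance-level or permutation procedure could sit in the unseen analysis plan. The authors themselves disclose that the split is not by individual.

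This limits the weight of the point: the primary analysis is unaffected by this defect. It does not withdraw the roles given to classification. Section 3.5.1 covers RMSSD, HF and LF, whereas 3.4.2 makes classification the means of showing significance for the ECG, EDR and fNIRS signals. The criticism is of what the text affirmatively claims, not of a test being left out. The admission in 3.5.2 is framed as a shortage of participants and is not carried into the claims. Explainable AI shows which features or regions the network used, but nothing in the article gives it a favourable direction.

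The numerical illustration is also open to fair criticism. The signals are mainly meant for pretrained CNNs and LSTMs, not KNN. The simulation used 60 segments instead of 1,980 and did not model the five-fold averaging. At ρ = 0.3 the pooled 20 v 10 accuracy (0.685) barely exceeds the majority class. The size of the inflation is therefore illustrative. Its direction is not in doubt whenever participants differ from one another, and the direction-free nature of the metrics needs no simulation at all.

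**Conclusion.** The concern holds, as a minor point confined to the role given to classification. The listed metrics cannot show benefit and are not a significance test; both statements follow from how the metrics are defined. Under a split that is not by individual, control-versus-treatment accuracy does not reliably show even that the arms differ. With no arm effect it averaged 0.50 to 0.96 for 10 v 10 as the assumed between-participant share ran from 0 to 0.7, and it returned to about 0.50 when whole participants were held out. The before/after contrast is distorted only if there is session-to-session variation within participants. The HRV analysis in 3.5.1 and the questionnaire and parameter analyses in 3.4 are not affected by this defect. What changes is what the trial may conclude from its deep-learning output.

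**What to change.** Make three wording changes.

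- **3.4:** remove *benefits* from the stated purpose of the classification analyses.
- **3.4.2:** delete the closing clause that has classification show significance.
- **3.5.3:** add a sentence such as: *Classifier results are exploratory and descriptive at segment level; they are not evidence of benefit or of a between-arm difference.*

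Rest any statement of benefit on the signed between-arm contrasts, with 95% confidence intervals, from the planned mixed model or ANCOVA on RMSSD and HF. State the favourable direction in advance where it can be justified. LF is also a primary outcome and should be reported in the same way, with a direction only if the authors can defend one. DASÖ-21, SCL, SCR and respiratory rate can serve as secondary or exploratory support.

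The contrasts use data and models already planned, with no new measurement or staff. The price is a narrower claim for the deep-learning results.

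Forming the five folds by participant would be a useful addition, though the wording fix is sound without it. With 10 per arm, each fold would hold out two participants per arm, and the result would be imprecise: at ρ = 0.5 with no arm effect, the central 95% of single hold-outs of that size ran from 0.35 to 0.68.
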